### Exclusion criteria

Participants will be excluded from the study if they decline to give informed consent to participate in the study or if they are hypersensitive or contraindicated to TST or IGRA.

#### Groups 2 and 3

Presumed TB disease with symptoms (cough, fever, night sweats, unintentional weight loss) and/or an abnormal CXR result suggestive of TB disease.Diagnosed with TB (microbiologically or clinically confirmed) in all forms or report having taken treatment for TB disease.History of TB infection (self-record or documented).

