**Methods and analysis:**

This cross-sectional study aims to assess the diagnostic accuracy for TB infection of the Cy-Tb skin test and Standard F TB assay (investigational tests) compared with the QuantiFERON-TB Gold Plus (QFT-Plus) assay as the immunological reference standard. Three different cohorts of study participants will be recruited at the Vietnam National Lung Hospital: adults with bacteriologically confirmed pulmonary TB (n=100), household contacts of people with TB (n=200) and people without TB infection (n=50). All consenting participants will undergo simultaneous testing with Cy-Tb, Standard F TB and QFT-Plus. The primary endpoint is the diagnostic accuracy of the Cy-Tb skin test and Standard F TB assay, expressed as sensitivity and specificity against the reference standard.

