## Introduction

### Background

 Tuberculosis (TB) is an infectious disease that is a leading cause of morbidity and mortality globally. There were an estimated 1.3 million total deaths caused by TB in 2022.^1^ Vietnam is one of the 30 highest TB burden countries, with an estimated 172 000 persons developing TB (including people living with HIV) in 2022.^2^

TB infection continues to be a significant cause of the increasing number of overall infections. After exposure to *Mycobacterium tuberculosis* (MTB), 5%–10% of people with TB infection will develop active TB, usually within the first 2 years after exposure.^3^ In 2018, the WHO estimated the global prevalence of TB infection to be 23%, meaning approximately 1.7 billion people were infected worldwide.^4 5^ A recent re-estimation using mathematical modelling demonstrated that in order to end TB by 2050, at least one-quarter of the global population living with TB infection would require TB preventive therapy.^6^

The tuberculin skin test (TST) and interferon-gamma (IFN-γ) release assays (IGRA) are currently the two preferred diagnostic tools for detecting TB infection. TST uses Tuberculin PPD RT 23 intradermally, which is affordable and easily performed.^7^ TST is currently the most frequently used TB infection test in Vietnam. However, TST has low sensitivity and specificity, particularly in people who are immunocompromised or have been BCG vaccinated, and people must return to a health facility to have the induration on their arm interpreted. IGRAs are more expensive and technically more complex, requiring phlebotomy, trained staff and laboratory equipment. Neither method is ideal for accurate and prompt diagnosis of TB infection in a community setting.^8^ Therefore, it is critical to develop new test methods to achieve the public health goal of preventing progression from TB infection to active TB and thereby reducing transmission.

Cy-Tb (Serum Institute of India, Pune, India) is an *M. tuberculosis* antigen-based skin test that was endorsed by the WHO in 2022.^9^ The test uses *M. tuberculosis*-specific antigens (rdESAT-6 and rCFP-10), which are injected intradermally, providing results after 48–72 hours, similar to the TST. However, a recent study indicated the superior performance of Cy-Tb compared with TST, with results in line with the QuantiFERON-TB Gold Plus (QFT-Plus) assay (QIAGEN, Venlo, The Netherlands).^10^

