### Laboratory procedures

After signing the Informed Consent Form (ICF) and undergoing eligibility assessment for study participation (including CXR, Xpert MTB/RIF Ultra and TB symptoms checklist), participants will undergo a baseline visit, followed by blood collection for Standard F TB and QFT tests. Subsequently, all participants will receive an injection of Cy-Tb (figure 1).

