**Figure 1 F1:**
[figure not shown]
Diagnostic accuracy study overview. QFT-Plus, QuantiFERON-TB Gold Plus; Standard F TB, STANDARD F TB-Feron FIA; TB, tuberculosis.

The CXR will be assessed by a single radiologist in the imaging department according to clinical routine and will be done prospectively and directly. The radiologist will be blinded to the Xpert MTB/RIF Ultra results.

10 mL of blood will be collected to three Standard F TB Tubes (Nil, TB Ag and the mitogen tube, 1 mL each tube) and four QFT-Plus tubes (Nil; TB1; TB2; Mitogen) for each participant, whereby the tubes will be incubated at the temperature of 37°C for a period of 16–24 hours. Standard F TB will be processed using the STANDARD F2400 equipment (SD Biosensor), an automated device. The ELISA test will be performed on QFT-Plus tubes. All tests will be processed and performed at the Vietnam National Reference Lab (VNRL)—National Lung Hospital. After being collected at the outpatient department at the same hospital, study samples will be transported to VNRL within 2 hours while still fresh. Lab personnel interpreting Standard F TB test results will be blinded to all other test results.

After blood collection, all participants will receive an intradermal injection of Cy-Tb and the results will be read after 48–72 hours. A solitary test dose of 0.1 mL comprises 0.05 µg each of rdESAT-6 and rCFP-10. These components elicit a delayed-type hypersensitivity reaction mediated by T lymphocytes. In individuals with previous mycobacterial exposure, this reaction results in induration at the injection site typically appearing within 48–72 hours, similar to the TST.^9^

In order to ensure the blinding of Standard F TB results to the reference test (QFT-Plus) and comparator test (Cy-Tb) and to the result of the microbiological reference standard including Xpert Ultra, different operators will be assigned and will be instructed to record results independently of other test results. Cy-Tb will be interpreted by a trained study nurse in the outpatient department.

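### The all-participant safety exclusion names TST, which nobody receives in this study, and omits Cy-Tb, which everybody is injected with

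*Protocol article*

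**What the plan says.** Exclusion criteria opens with two grounds that apply to all three groups. One is refusal of consent. The other removes people "if they are hypersensitive or contraindicated to TST or IGRA". Further exclusions follow for Groups 2 and 3 only.

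The tests given are stated three times. The abstract says: "All consenting participants will undergo simultaneous testing with Cy-Tb, Standard F TB and QFT-Plus". Laboratory procedures says, after describing blood collection: "Subsequently, all participants will receive an injection of Cy-Tb". The same section, in the text after Figure 1, repeats it: "After blood collection, all participants will receive an intradermal injection of Cy-Tb".

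The Background keeps the two skin tests apart. On the first it says "TST uses Tuberculin PPD RT 23 intradermally". Cy-Tb is introduced as a different product, an "antigen-based skin test that was endorsed by the WHO in 2022", containing rdESAT-6 and rCFP-10.

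**The concern.** An eligibility criterion about hypersensitivity or contraindication exists to keep people away from a product that may harm them. It can do so only if it names the product they will be given. Here the criterion names TST, and the study injects Cy-Tb.

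A screener who applies the sentence literally makes two errors. A candidate with a problem specific to tuberculin is turned away, although the study would never expose that person to tuberculin. A candidate with a known hypersensitivity or contraindication to Cy-Tb or its components is not turned away, although the study will inject it. At stake are the safety screen for the investigational injection and a clear definition of who is eligible.

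**Working it through.** No arithmetic applies: the point depends on no rate, power or sample-size figure. The check is a comparison of the criterion with the rest of the article.

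**1. Criterion against tests given**

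| Test | Named in the all-participant exclusion? | Given in the study? |
|---|---|---|
| TST (tuberculin PPD RT 23) | Yes | No |
| Blood assays (Standard F TB, QFT-Plus) | Yes, through the word IGRA | Yes, to all |
| Cy-Tb, intradermal | No | Yes, to all |

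The IGRA half of the criterion fits the procedures. The skin-test half does not. The mismatch falls on the only test that puts a product into the participant's body, since the other two are run on drawn blood.

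**2. Does the study give a TST anywhere?** No. TST appears in the Background as a current test and as the reference standard of an earlier study. It appears in Laboratory procedures as a comparison for the timing of the Cy-Tb reaction, and it appears in the exclusion. It is absent from the abstract's list of tests, from Laboratory procedures as a test performed, and from the Data analysis plan.

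**3. Can TST be read as including Cy-Tb?** Not in the article's own terms. The Background gives the two different antigens and contrasts their performance. Laboratory procedures calls the Cy-Tb response similar to that of the TST, which treats them as two tests.

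**4. Does another section supply the missing screen?**
- Inclusion criteria: age, consent, residence and group-specific TB status. Nothing on Cy-Tb tolerance.
- Exclusions for Groups 2 and 3: symptoms or abnormal chest X-ray, TB disease or its treatment, and history of TB infection. Nothing on Cy-Tb tolerance.
- Laboratory procedures: eligibility assessment is said to include chest X-ray, Xpert Ultra and a symptom checklist. The list may not be complete, but nothing in it concerns Cy-Tb tolerance.
- Safety: recording and management of reactions after the injection, not screening before it.
- Safety considerations: the added risk is called minimal, and no screen is added.

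No section repairs the criterion.

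**5. Reach.** The criterion and the injection both apply to all participants, so the mismatch covers 100 + 200 + 50 = 350 people.

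**The case against.** The strongest reply is that TST is shorthand for intradermal skin testing. The article likens Cy-Tb to the TST twice, trained staff would probably understand the intent, and product-specific contraindications are the kind of detail that a journal article leaves to the full protocol. The expected harm is also small. The article calls the added risk minimal and describes the common reactions as mild. It says the tests are not yet in programme use, so few candidates will have met Cy-Tb before.

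Part of this stands. The document does not show that anyone would be wrongly injected, and the practical risk may be low. The defence by condensation does not stand, because the article does not leave the criterion out. It states the criterion and names a test that is not performed. The shorthand reading goes against the Background's own definition of TST. Low prior exposure to Cy-Tb limits how often a known reaction would be on record, but a contraindication can apply to someone who has never received the product.

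A reader might also infer something stronger: that being hypersensitive to TST means having had a positive TST. Laboratory procedures says of the Cy-Tb antigens "These components elicit a delayed-type hypersensitivity reaction mediated by T lymphocytes", which uses the same word for an ordinary positive response. On that reading, Group 1 would lose likely Cy-Tb reactors and its sensitivity estimate would be biased downward. The document does not support this inference, for four reasons.
- The same phrase also covers IGRA, a blood test, for which a skin reaction makes no sense, and it is paired with contraindication. Both point to a tolerability criterion.
- A history of TB infection is excluded separately, and only for Groups 2 and 3. That line would be largely redundant if the general criterion already meant past positivity.
- Excluding past reactors would work against Group 1's stated purpose, which is to measure sensitivity in confirmed TB.
- The sentence in Laboratory procedures describes how Cy-Tb works and does not define an eligibility term.

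The article also gives no share of Group 1 with a past TST result, so any figure for such a bias would have no basis in the document.

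**Conclusion.** The contradiction holds: the skin-test half of an operative safety exclusion refers to a product the study does not use and leaves out the only product it injects. This is a wrong stated rule and not a missing detail.

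Its size is not numerical. No shift in sensitivity or specificity is claimed, and the primary and secondary endpoints stand as they are. The conclusion rests on the article alone. If the full protocol or the screening form already names Cy-Tb, the fault lies in the published criterion only, and still needs correcting there. The point deserves action because it bears on participant safety and is cheap to put right. It does not threaten the trial's analysis.

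**What to change.** Reconcile the all-participant sentence in Exclusion criteria, and the matching item on the screening form, with the tests listed in the abstract and in Laboratory procedures, so that the criterion refers to the products administered in this study. Which hypersensitivities or contraindications to list is a clinical matter for the sponsor to set.

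The cost is one sentence in the eligibility criteria and the corresponding form entry. Sample size, procedures and analysis do not change.

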### Sample size

Sample size calculations used estimates from previously published studies on the sensitivity and specificity of Cy-Tb and Standard F TB,^10 13^ incorporating the prevalence of the disease. These calculations were based on the sample size calculation formula for sensitivity and specificity.^16^

#### Group 1

We assumed a true sensitivity of the Cy-Tb test and Standard F TB assay of 75.8% and 88.9%, respectively,^13^,^17^ with a precision of 0.1 for the related 95% CI and drop-out rate (lost to follow-up (LTFU)) of 10%. The smallest sample size to evaluate the sensitivity and specificity of the Cy-Tb test and Standard F TB assay in the group are 71 participants and 38 participants, respectively.

#### Group 2

We assumed a proportion of TB infection among group 2 of 50%,^18^ a true sensitivity of the Cy-Tb test and Standard F TB assay of 75.8% and 88.9% respectively,^13 17^ with a precision of 0.1 for the related 95% CI and drop-out rate (LTFU) of 10%. The smallest sample size to evaluate the sensitivity and specificity of the Cy-Tb test and Standard F TB assay in the group is 158 participants and 85 participants, respectively.

#### Group 3

We assumed a proportion of TB infection among group 3 of 5%, a true specificity of the Cy-Tb test and Standard F TB assay of 98.1% and 92.5% respectively,^13 17^ with a precision of 0.1 for the related 95% CI and drop-out rate (LTFU) of 10%. The smallest sample size to evaluate the specificity of the Cy-Tb test and Standard F TB assay in the group is 8 participants and 29 participants, respectively.

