### Data analysis plan

Points estimates of sensitivity and specificity with 95% CI will be calculated based on Wilson score methods to accommodate for the loss of coverage in small samples. The Cy-Tb and Standard F TB test index accuracy will be evaluated to fit with the case definition and results compared with the QFT-Plus reference standard test results presented in table 1.

**Table 1 T1:** The case definition and results

	Definitions			
Test results		Tuberculosis infection	Not infected	Total
	Detected	True positive	False positive	True positive+false positive
	Not detected	False negative	True negative	False negative+true negative
	Total	True positive+false negative	False positive+true negative	Total

Concordant with the methods employed in a systematic review by WHO, we consider the rate of negative results to represent proxy specificity regardless of TB incidence and estimates.^20^ Differences in proportion of negative results between investigated tests and the reference test will be calculated. In addition, we will also calculate the rate of negative results on the Cy-Tb and Standard F TB tests among QFT-Plus negative participants.

Sensitivity is the percentage of participants with positive study tests among those with microbiologically confirmed TB (group 1).

Specificity is the percentage of participants with negative study tests among those at low risk for TB infection (group 3). We will also calculate the proportion of people with negative index tests among those at risk for TB infection (group 2).

The descriptive statistics will be calculated for the sample and the contingency table will be created to evaluate the diagnostic performance, including sensitivity, specificity and associated 95% CI for the Cy-Tb test and Standard F TB assay in comparison with the reference standard. The area under the curves, that is, areas under the receiver-operating characteristics curve will be calculated to estimate the comparative diagnostic accuracy of the Cy-Tb test and Standard F TB assay and QFT-Plus.

Multiple multivariate logistic regression models will be performed to adjust for confounders while analysing associations between participants characteristics and test accuracy. Subgroup analysis of test accuracy in different groups will be done with regard to gender, age, BMI, comorbidities, TB exposure, etc.

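### Sample size: the Group 1 minima leave out the 10% drop-out listed among their inputs, the Group 3 minima do not follow from all their inputs, and 8 participants do not give 0.1 precision by Wilson

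*Protocol article*

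**What the plan says.** All figures are in the protocol article, Sample size section. For Group 1 the inputs are "We assumed a true sensitivity of the Cy-Tb test and Standard F TB assay of 75.8% and 88.9%, respectively", and the calculation is made "with a precision of 0.1 for the related 95% CI and drop-out rate (lost to follow-up (LTFU)) of 10" per cent. The resulting minima are stated as "in the group are 71 participants and 38 participants, respectively". The sentence says they serve both sensitivity and specificity, although the paragraph gives no specificity input.

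Group 2 uses the same sensitivities, precision and drop-out, and adds a prevalence: "We assumed a proportion of TB infection among group 2 of 50" per cent. The minima are "in the group is 158 participants and 85 participants, respectively".

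Group 3 assumes specificities of 98.1% (Cy-Tb) and 92.5% (Standard F TB), the same precision and drop-out, and "We assumed a proportion of TB infection among group 3 of 5" per cent. The minima are "in the group is 8 participants and 29 participants, respectively".

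The Data analysis plan sets the interval method: "Points estimates of sensitivity and specificity with 95% CI will be calculated based on Wilson score methods", with small samples as the reason. The Study population section plans 100, 200 and 50 participants in Groups 1, 2 and 3.

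**The concern.** The three paragraphs list the same drop-out allowance, so the same inflation should appear in all three results. It appears in Group 2 and not in Group 1, and the Group 3 figures fall short of what their inputs imply. Separately, a minimum of 8 participants for a specificity near 98% looks too small for a precision of 0.1 by any small-sample interval, and the plan chooses Wilson because of small samples.

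These minima are the only quantitative support for precision in the document, which does not say what precision 100/200/50 will deliver. A reader would take 71 as already covering losses, and 8 as enough for a specificity estimate. Neither is so.

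**Working it through.** **Inputs.** From Sample size: sensitivities 0.758 and 0.889; specificities 0.981 and 0.925; precision d = 0.1; drop-out 0.10; prevalence 0.50 (Group 2) and 0.05 (Group 3). For a 95% interval z = 1.96. Precision is read as a half-width, the reading that reproduces the plan's figures.

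**Formula.** n0 = z²·p(1−p)/d². Divide by prevalence for sensitivity or by (1 − prevalence) for specificity, then by 0.9 for drop-out.

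**Group 1.**
- Cy-Tb: 1.96² × 0.758 × 0.242 / 0.01 = 70.47 → 71, the stated figure. With drop-out, 70.47/0.9 = 78.3 → 79.
- Standard F TB: 1.96² × 0.889 × 0.111 / 0.01 = 37.91 → 38, the stated figure. With drop-out, 37.91/0.9 = 42.1 → 43.
- Multiplying by 1.1 instead of dividing by 0.9 gives 78 and 42. No drop-out variant gives 71 and 38.

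**Group 2.**
- Cy-Tb: 71/0.5 = 142; 142/0.9 = 157.8 → 158, as stated.
- Standard F TB: 38/0.5 = 76; 76/0.9 = 84.4 → 85, as stated.
- Drop-out is therefore included here.

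**Group 3.**
- Cy-Tb: n0 = 7.16; 7.16/0.95 = 7.54 → 8, as stated, without drop-out. With both inputs, 7.54/0.9 = 8.4 → 9.
- Standard F TB: n0 = 26.65; 26.65/0.95 = 28.05 → 29, as stated, without drop-out. With both inputs, 28.05/0.9 = 31.2 → 32.
- Rounding up at every step, as 158 requires, gives 10 and 33 instead of 9 and 32.
- A second route also gives the stated figures: ignore prevalence, multiply by 1.1 and round to nearest (7.16 × 1.1 = 7.88 → 8; 26.65 × 1.1 = 29.3 → 29). Either way one listed input is unused.

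**Precision by Wilson.** Half-width = z·√[p(1−p)/n + z²/(4n²)] / (1 + z²/n), evaluated at the assumed proportion.

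| Assumed p | n | Normal approx. | Wilson |
|---|---|---|---|
| 0.981 | 8 | 0.095 | 0.174 |
| 0.925 | 29 | 0.096 | 0.103 |
| 0.758 | 71 | 0.100 | 0.098 |
| 0.889 | 38 | 0.100 | 0.102 |

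Even 8 negatives out of 8 give a Wilson interval of 67.6% to 100%, a half-width of 0.162. Only the figure of 8 misses materially.

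**Minima for a Wilson half-width of at most 0.1.** Evaluable numbers needed are 68 (p = 0.758), 40 (0.889), 19 (0.981) and 31 (0.925). Hence:
- Group 1: 68/0.9 = 75.6 → 76; 40/0.9 = 44.4 → 45.
- Group 2: 68/0.5/0.9 = 151.1 → 152; 40/0.5/0.9 = 88.9 → 89.
- Group 3: 19/0.95/0.9 = 22.2 → 23; 31/0.95/0.9 = 36.3 → 37.

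**Wilson half-widths from the planned sizes after 10% loss.**
- Group 1: 100 × 0.9 = 90, giving 8.7 points (Cy-Tb) and 6.6 points (Standard F TB).
- Group 3: 50 × 0.9 = 45, of whom about 42 are uninfected (45 × 0.95 = 42.75), giving about 5.6 and 8.4 points; 5.4 and 8.1 if all 45 are counted.

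**The case against.** The strongest reply is that nothing in the design depends on these minima. Enrolment is fixed at 100/200/50, above every corrected figure on either basis. A reader might infer from the understated minima that the study is too small, or that 71 or 8 would serve as an acceptable floor if recruitment fell short. The document supports neither: the planned sizes meet the 0.1 precision, and no section makes the minima a fallback or stopping point. Even in Group 1 itself, a 10% loss from 71 and 38 leaves about 64 and 34 participants and Wilson half-widths of about 0.103 and 0.108, a miss of less than one percentage point. This reply stands and limits the point to a minor one.

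It is also tempting to say that Group 3 certainly omits drop-out. That is the closest match to the plan's method, but it is not proven. Leaving out prevalence reproduces 8 and 29 too, and no single rounding rule gives both 158 in Group 2 and 8 in Group 3. What stands is that the figures do not use all the stated inputs.

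Planning with a normal approximation and analysing by Wilson is common, and for 29, 71 and 38 the two nearly agree. That stands as well. It does not rescue 8, where the half-width is 0.174.

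On the Group 1 wording, one might go further and say that specificity cannot be obtained in confirmed cases. Objective 1 uses QFT-Plus as reference in this group, so QFT-negative cases would supply a denominator. The supportable point is narrower: that paragraph gives no specificity input, and the Study population section and the Data analysis plan give Group 1 to sensitivity.

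**Conclusion.** The point holds as a minor correction of stated figures. By the plan's own formula the Group 1 minima are understated by 8 (71 against 79) and 5 (38 against 43), because the listed 10% drop-out was not applied, while Group 2 applied it. Group 3 is understated by 1 and 3 (8 against 9, 29 against 32) with one rounding at the end; which input was omitted is not known. The figure of 8 also fails the stated precision under the planned interval, by about 7 percentage points.

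This rests on reading 0.1 as a half-width and on evaluating Wilson at the assumed proportions. Observed counts will vary: 18 negatives out of 19, for example, give a half-width of 0.118. Group 1's omission is certain on these inputs. The adequacy of the planned enrolment is not in question.

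**What to change.** Restate the minima on one consistent basis and name it.
- Normal approximation with drop-out: 79/43 (Group 1) and 9/32 (Group 3), with Group 2 left at 158/85.
- Wilson, preferable because it is the analysis interval: about 76/45 (Group 1) and 23/37 (Group 3). If this basis is chosen, Group 2 becomes 152/89 so that all groups match.

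Add one sentence giving the Wilson half-widths that the planned sizes deliver after 10% loss: about 8.7 and 6.6 points in Group 1 (n = 90), and about 5.6 and 8.4 points in Group 3 (about 42 uninfected). Remove the mention of specificity from the Group 1 sentence.

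The cost is a text edit. Enrolment and analysis do not change.
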